### Statistical analysis

#### Sample size determination

The inclusion of 32 participants (16 in each group) would give the study 80% power to detect a clinically significant additional increase of 22% in BMD with WBV (assuming a 9% increase of BMD in the PTH 1-34-alone group and 11% increase in the combined PTH 1-34 + WBV group, and assuming a standard deviation (SD) of the BMD increase of 2% [12]. Inclusion of 40 participants (20 in each group) will allow for a 20% dropout rate.

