### Endpoints

#### Primary endpoints

The primary endpoint is the percent change in areal BMD of total hip and lumbar spine as measured by dual-energy x-ray absorptiometry (DXA) (Hologic Discovery, Waltham, MA, USA) from baseline until 12 months (Table 2).

**Table 2 Tab2:** Primary and secondary endpoints

	Measurement	Site	Time (months)
Primary endpoints			
Δ Bone mineral density	DXA	Total hip Spinal region	12
Secondary endpoints			
Δ Bone mineral density	DXA	Total hip Spinal region	6, 18, and 24
Δ Bone microarchitecture	HR-pQCT	Distal radius Distal tibia	6, 12, 18, and 24
Δ Bone biomarkers	P1NP CTX, sclerostin	Serum	3, 6, 12, 18, and 24
Δ Physical biomarkers	TUG SPPB		3, 6, 12, 18, and 24
	Dynamometer	Hand grip	
	Nottingham power rig	Leg extensor	
Δ Quality of life	EQ-5D		12 and 24
Δ Fear of falling	FES-I		12 and 24
Physical activity	IPAQ		0, 12, and 24
Adherence to WBV	Training logbook		Continuously
Falls	Falls calendar		Continuously

*Δ* change from baseline; Time is measured in months; *DXA* dual-energy x-ray absorptiometry; *HR-pQCT* high-resolution peripheral quantitative computed tomography; *P1NP* procollagen type-1 amino-terminal propeptide; *CTX* carboxy-terminal type-1 collagen crosslinks; *TUG* Timed Up and Go; *SPPB* Short Physical Performance Battery; *FES-I* Falls Efficacy Scale International; *IPAQ* The International Physical Activity Questionnaire; *EQ-5D* EuroQoL 5-dimension, 5-level questionnaire, *WBV* whole-body vibration

BMD is chosen as an endpoint since it is an important determinant of fracture risk and is used to diagnose and assess response to treatment in osteoporotic patients [1, 21].

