#### Statistical methods and data managing

The intervention arm (PTH + WBV) is compared against the control arm for all primary analyses. We will use analysis of covariance (ANCOVA) and “percentage change” for primary outcome adjusting for baseline measurements. For secondary outcomes we will use a chi-squared test for binary outcomes, analysis of variance (ANOVA) and the *T* test for continuous outcomes, and for non-normally distributed continuous outcomes we will use log transformation or Wilcoxon’s match-pairs signed-rank test and the Kruskal-Wallis test.

All *p* values will be reported to four decimal places with *p* values < 0.001 reported as *p* < 0.001. STATA version 14 will be used to conduct analyses. For all tests, we will use two-sided *p* values with an alpha ≤ 0.05 level of significance.

The analyses will be conducted with the intention-to-treat method, and in order to investigate the effect of adherence and withdrawal a per-protocol analysis will be conducted. Missing data will be handled using multiple imputation. Study data is collected and managed using REDCap (Version 6.5.10 – © 2015 Vanderbilt University) electronic data capture tools hosted at the University of Southern Denmark [44]. Sequential study numbers will be allocated to study patients and entered into the recruitment log at the secure web database REDCap.

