## Discussion

This is a RCT in osteoporotic patients randomized to PTH 1-34 treatment alone or to combined PTH 1-34 treatment and WBV. The primary and secondary endpoints in the study are chosen because previous studies have shown such markers of bone mass, microarchitecture, and turnover, as well as indices of physical performance, to be associated with osteoporosis or fragility fractures.

Earlier studies have reported WBV as a feasible intervention [12] and in older patients the adherence is reported to be good [19].

The intervention is designed to be of long duration (12–24 months) and the setting at the participants’ own home makes the training easy and highly accessible.

The study has limitations including the non-blinded design. It is our hypothesis that the primary endpoint, the BMD as well as a number of secondary endpoints (bone microarchitecture and bone turnover markers) are not at risk of bias by the open-label design. The functional biomarkers on the other hand could be affected by the non-blinded design but the study personnel performing the tests are blinded to the allocation and the baseline data is collected before randomization.

Measurements of quality of life, physical activity, and the FES-I questionnaire are patient-collected data, resulting in the possibility of bias in the reporting.

To limit the possibility of bias by attention, the participants will receive close to an equal amount of contacts by the investigators because of the “at home training design.”.

The study is partially blinded and is protected against selection bias by central randomization after baseline measurements, randomization via web with no stratification, and by allocation concealment.

It is our hypothesis that the DXA, HR-pQCT, and bone marker measurements are not at risk of performance bias. The physical biomarkers may be prone to performance bias, but the test personnel will be blinded to avoid evaluation bias.

To avoid attrition in both arms and ensure adherence, the participants are contacted by telephone each month during the first year and every third month during the second year. The participants receive a direct telephone number and mailing address to the primary investigator and are encouraged to make contact in case of any questions or events.

Every patient is motivated to attend follow-up regardless of randomization or adherence. The participants do not receive payment but are reimbursed for transport expenses.

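### The 80% power is for one test at one unnamed BMD site, while the primary endpoint covers total hip and lumbar spine with no rule for what counts as success

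*Protocol article*

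**What the plan says.** Under Primary endpoints, the protocol article says: "The primary endpoint is the percent change in areal BMD of total hip and lumbar spine", from baseline to 12 months. Table 2 lists the same two sites. The heading there is plural and the sentence is singular.

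Under Sample size determination, 32 participants (16 per arm) "would give the study 80% power to detect a clinically significant additional increase of 22% in BMD with WBV". The inputs follow in the same sentence: "assuming a 9% increase of BMD in the PTH 1-34-alone group", 11% in the combined arm, and an SD of 2%. No site is attached to any of them. Enrolment is raised to 40 for 20% dropout.

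Under Statistical methods and data managing, the primary analysis is ANCOVA on percentage change, "for primary outcome adjusting for baseline measurements". On error control the section says "For all tests, we will use two-sided" p values "with an alpha ≤ 0.05 level of significance". It gives no success rule for hip and spine together and no allocation of alpha between them.

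**The concern.** The paragraph attributes 80% power to the study, but the calculation behind it is one comparison of two means at full alpha. A study with two primary sites has no single power until it is fixed what counts as a positive result.

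The three natural rules pull in different directions. Requiring both sites lowers power. Dividing alpha lowers power at each site but leaves two chances of success. Letting either site count at 0.05 raises power but also raises the type I error above 5%.

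Two things are at stake. A null result could be read as coming from a trial with 80% power when, under the rule finally applied, it had less. A positive result at one site only could be claimed at a nominal 5% when the true error rate is higher.

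The missing site label adds to this. One mean difference and one SD serve two anatomical sites, so a reader cannot tell which site the 80% belongs to.

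**Working it through.** **Inputs from the article.** Control-arm gain 9%, combined-arm gain 11%, SD 2%, 16 evaluable per arm, 20% dropout, two-sided alpha 0.05.

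**Assumptions, not in the article.** The same difference and SD at hip and spine; correlation ρ between hip and spine change of 0 to 0.8.

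**Step 1: reproduce the stated figure.**
- Difference: 11 − 9 = 2 percentage points. Standardised effect: 2/2 = 1.
- Normal formula: n = 2 × (1.960 + 0.842)² / 1² = 15.7, so 16 per arm.
- Power at 16 per arm: Φ(√(16/2) − 1.960) = Φ(2.828 − 1.960) = 80.7%.
- Noncentral t: df = 30, noncentrality 2.828, critical value 2.042, power 78.1%. One degree of freedom fewer for the baseline covariate gives 78.0%.
- Dropout: 32/0.8 = 40.
- The 22%: 2/9 = 22.2% of the control-arm gain.

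The arithmetic is sound for one test.

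**Step 2: both sites must reach p < 0.05.** The power is the probability that both correlated test statistics exceed the critical value. It comes from simulated t-tests, and from the bivariate normal distribution for comparison.

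| ρ | both sites, t | both sites, normal |
|---|---|---|
| 0 | 61% | 65% |
| 0.3 | 64% | 68% |
| 0.5 | 66% | 70% |
| 0.7 | 69% | 72% |
| 0.8 | 71% | 74% |

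At ρ = 0 the check by hand is 0.781² = 0.61 and 0.807² = 0.65.

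**Step 3: alpha split, 0.025 per site.**
- A given site, normal: Φ(2.828 − 2.241) = 72.1%. Noncentral t: 68.0%.
- At least one site, t: 90% (ρ = 0), 86% (0.3), 83% (0.5), 80% (0.7), 78% (0.8). A rerun with one million trials put the last value at 77.5%. Familywise error stays at or below 5%.
- Hochberg's procedure, at least one site, t: 91%, 87%, 84%, 81% and 79% at the same correlations.

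**Step 4: either site suffices at 0.05, unadjusted.** Familywise error is 1 − 0.95² = 9.75% at ρ = 0, 9.1% at 0.5 and 7.8% at 0.8.

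**Step 5: one site named first, the other tested only if the first succeeds.** Power for the first site is the stated figure (80.7% normal, 78.1% t). Power for both is as in Step 2.

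**The case against.** The strongest reply is that nothing is miscalculated. The sample size, the dropout inflation and the 22% all reproduce, and the gap between 78% and 80% is only a choice of formula. That stands, and the point does not rest on it: by the normal formula that favours the plan, both-site power is still 65–74% and per-site power at 0.025 is 72%.

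The baseline-adjusted ANCOVA may recover some power. If baseline and percent change correlate at 0.3 (an assumption), one-site power at 16 per arm is 81.7%. If nobody drops out, 20 per arm gives 87% at 0.05 and 79% per site at 0.025 (t), and 78–84% for both sites (normal). The shortfall therefore applies to the planned 32 evaluable participants.

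It can also be said that a success rule belongs in an analysis plan that is not shown. That would answer a complaint of mere omission. Here, though, the article itself states a power for the whole study and a 0.05 level for every test, and the power figure fits its two-site endpoint only under some rules.

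A reader might go further than the document allows, in four ways:
- That the design delivers only 61–71% power. Nothing says both sites must succeed, and the range needs equal effects and a correlation that the article does not give.
- That no rule preserving 5% reaches 80%. This is untrue: a 0.025 split with one site sufficing gives about 80% or more up to a correlation of about 0.7, and naming one site first keeps the stated figure.
- That the 22% is an error. It is a correct relative figure, loosely worded; the 9% and 11% follow at once and the sample size is unaffected.
- That the SD of 2% comes from an unsuitable source or is too small. The cited study cannot be seen, and the article offers no figure from which to argue for a larger SD or a smaller effect.

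**Conclusion.** The point holds as a mismatch between the power claim and the primary endpoint. The 80% is correct for one test at one unnamed site. It is not a power for a two-site endpoint whose success rule is undefined.

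The consequence depends on the rule. Requiring both sites costs roughly 7 to 17 points against the one-site t figure (78% down to 71–61%). Splitting alpha costs about 10 points at a given site (78% to 68%) but leaves about 78–90% for at least one. Leaving either site to count at 0.05 raises the familywise error to about 8–10%.

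These sizes rest on equal effect and SD at both sites, a correlation of 0 to 0.8, and 16 evaluable per arm. The mismatch itself needs none of these assumptions.

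**What to change.** In Sample size determination and Statistical methods and data managing:

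1. State the success rule for hip and spine: both required; or either, under a procedure that holds familywise error at 5% (Hochberg, or 0.025 per site); or one site named as primary with the other tested second.
2. Name the site to which the 9%, 11% and SD 2% refer.
3. Restate the power under the chosen rule for the planned 32 evaluable participants, saying what is assumed for the other site.
4. Word the target as 2 percentage points (22% of the control-arm gain).

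The rule should be fixed before outcome data are compared by arm. The cost is the rewording of a few sentences, with no change to the sample size. The drawback is that the stated power may become less favourable, most of all if both sites are required.

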#### Statistical methods and data managing

The intervention arm (PTH + WBV) is compared against the control arm for all primary analyses. We will use analysis of covariance (ANCOVA) and “percentage change” for primary outcome adjusting for baseline measurements. For secondary outcomes we will use a chi-squared test for binary outcomes, analysis of variance (ANOVA) and the *T* test for continuous outcomes, and for non-normally distributed continuous outcomes we will use log transformation or Wilcoxon’s match-pairs signed-rank test and the Kruskal-Wallis test.

All *p* values will be reported to four decimal places with *p* values < 0.001 reported as *p* < 0.001. STATA version 14 will be used to conduct analyses. For all tests, we will use two-sided *p* values with an alpha ≤ 0.05 level of significance.

The analyses will be conducted with the intention-to-treat method, and in order to investigate the effect of adherence and withdrawal a per-protocol analysis will be conducted. Missing data will be handled using multiple imputation. Study data is collected and managed using REDCap (Version 6.5.10 – © 2015 Vanderbilt University) electronic data capture tools hosted at the University of Southern Denmark [44]. Sequential study numbers will be allocated to study patients and entered into the recruitment log at the secure web database REDCap.

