##### Bone microarchitecture

Images from high-resolution peripheral quantitative computed tomography (HR-pQCT) (Xtreme CT, Scanco Medical, AG, Brüttisellen, Switzerland), of the non-dominant distal radius and distal tibia (the opposite limb in the presence of a previous fracture) will be obtained to measure bone geometry, cortical morphology, trabecular morphology, and overall biomechanical competence. In in-vitro studies estimated bone strength of the radius using finite element analysis [22, 23] which has been shown to be more closely correlated to observed radius bone strength than areal BMD by DXA [22]. PTH 1-34 treatment has been shown to be associated with an increase in vertebral estimated bone strength [24] and preservation of the estimated bone strength of the radius and hip [25, 26]. The images are obtained at baseline, 6, 12, 18, and 24 months (Table 2). The reported outcomes will be total BMD, cortical thickness, cortical porosity, bone volume per trabecular volume (BV/TV), trabecular number, trabecular thickness, and finite element failure load. The scanning protocol and the image acquisition have previously been described in detail [22, 23].

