##### Serum bone turnover markers

Markers of bone formation (procollagen type-1 amino-terminal propeptide (P1NP)) and bone resorption (carboxy-terminal type-1 collagen crosslinks (CTX-1) will be measured by the method of chemiluminescence (iSYS, Immunodiagnostic Systems Ltd., Boldon, England). Sclerostin is analyzed using TECOmedical Human Sclerostin HS ELISA (TECOmedical group, Sissach, Switzerland). Bone turnover is affected by treatment with PTH 1-34, and studies have shown that a rise in the marker of bone formation, P1NP, during PTH 1-34 treatment is a predictor of the increase in BMD [27]. The assessment of bone biomarkers will allow exploration of mechanisms of action of WBV in augmenting PTH 1-34 treatment on bone turnover. The blood samples are taken at baseline, 3, 6, 12, 18, and 24 months (Table 2) after an overnight fast and stored at − 70 °C until analyzed in a central laboratory.

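### Baseline adjustment is stated for the primary outcome only; continuous secondary outcomes get a t-test or ANOVA although their baselines are collected, which costs precision

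*Protocol article*

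**What the plan says.** All of this is in the protocol article.

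- **Primary outcome.** Under *Statistical methods and data managing*, ANCOVA on percentage change is planned "for primary outcome adjusting for baseline measurements".
- **Secondary outcomes.** The next sentence begins "For secondary outcomes we will use a chi-squared test for binary outcomes, analysis of variance (ANOVA". For continuous variables the named methods are "analysis of variance (ANOVA) and the *T* test for continuous outcomes", with log transformation or rank tests where the data are not normal. No baseline covariate is mentioned.
- **Scale.** Table 2 (*Primary endpoints*) marks BMD, HR-pQCT, bone markers, functional tests, EQ-5D and FES-I with Δ, which its footnote explains as "change from baseline; Time is measured in months". IPAQ carries no Δ but is listed at month 0 as well as 12 and 24.
- **Baselines.** For HR-pQCT, "The images are obtained at baseline, 6, 12, 18, and 24 months". For bone markers, "The blood samples are taken at baseline, 3, 6, 12, 18, and 24 months". *Functional biomarkers* and *Questionnaires* also include a baseline assessment.
- **BMD.** Total hip and lumbar spine BMD is primary at month 12 and secondary at 6, 18 and 24 months (*Bone mass* and Table 2).
- **Size.** *Sample size determination* counts on 16 evaluable women per group, with 20 per group randomized. *Randomization* states that there is no stratification.

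**The concern.** Two adjacent sentences fix two methods for the same kind of variable, and the article gives no reason for the difference. It shows most plainly in BMD, where one measure at one site changes its analysis with the visit. The secondary estimates would then not be directly comparable with the primary one.

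Two things are at stake in so small a trial. First, subtracting baseline is in general a less efficient use of it than fitting it as a covariate, so confidence intervals for the secondary outcomes may be wider than the collected data allow. Second, randomization is unstratified and the arms are small, so they can differ at baseline by chance. A change score over-corrects for such a difference: the arm that starts higher tends to show the smaller change through regression to the mean, whatever the treatment does.

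**Working it through.** **1. The plan's own figure.** Inputs from *Sample size determination*: difference 11 − 9 = 2 points, SD 2, two-sided alpha 0.05, power 80%.

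n per group = 2 × (1.960 + 0.842)² × (2/2)² = 15.7, rounded up to 16. Then 32/(1 − 0.20) = 40. The stated sizes reproduce. Using the t distribution gives 16.7, that is 17 per group, and 78.1% power at 16, which is close enough. This calculation concerns the primary outcome and the present point leaves it untouched. It supplies the 16 per group used below.

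**2. Precision.** Assume equal variance s² at baseline and follow-up, and correlation r between them.

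- Variance of a change score: 2s²(1 − r)
- Residual variance under ANCOVA: s²(1 − r²)
- Ratio, ANCOVA to change: (1 + r)/2
- Extra patients needed by the change-score t-test: 2/(1 + r) − 1

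The article gives no 12-month r, so a range is shown. The power column supposes that the change-score t-test has 80% power at 16 per group (30 df, noncentrality 2.895). For ANCOVA the noncentrality is divided by √[(1 + r)/2 × 29/28], with 29 df. The factor 29/28 = 1 + 1/28 is a small-sample allowance for estimating the slope.

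| Assumed r | Variance ratio | Extra patients for t-test on change | ANCOVA patients matching 32 | ANCOVA power |
|---|---|---|---|---|
| 0.5 | 0.75 | 33% | 24.0 | 88.8% |
| 0.7 | 0.85 | 18% | 27.2 | 84.7% |
| 0.9 | 0.95 | 5% | 30.4 | 80.5% |
| 0.95 | 0.975 | 2.6% | 31.2 | 79.5% |

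The middle columns ignore the small-sample allowance; the power column includes it. By r = 0.95 the lost degree of freedom and the allowance offset the gain.

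The formulas are for absolute change. For percentage change they are an approximation.

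**3. IPAQ.** With no Δ in Table 2, its follow-up values may be compared directly. The variance ratio is then 1 − r², and the extra patients needed are 1/(1 − r²) − 1, which is 33% at r = 0.5 and 96% at r = 0.7.

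**4. Chance imbalance.** One standard error of the baseline difference is √(2/16) = 0.35 SD with 16 per arm and √(2/20) = 0.32 SD with 20. Given that imbalance, the change-score contrast shifts by (1 − r) times it:

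| Assumed r | Shift, 16 per arm | Shift, 20 per arm | Shift in standard errors of the change contrast, √[(1 − r)/2] |
|---|---|---|---|
| 0.5 | 0.18 SD | 0.16 SD | 0.50 |
| 0.7 | 0.11 SD | 0.09 SD | 0.39 |
| 0.9 | 0.04 SD | 0.03 SD | 0.22 |

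ANCOVA removes this shift when the relation to baseline is linear.

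**The case against.** **The existing method is valid.** Most secondary outcomes are changes from baseline, so baseline is already used. Under randomization the t-test on change is unbiased on average and keeps its error rate. This stands. A reader might infer that the secondary analyses ignore baseline or are invalid, but Table 2 does not support that. The shift in step 4 is conditional on an imbalance that may not occur.

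**The size rests on an assumed r.** This stands too. The only repeatability correlation in the article is 0.97 for leg extensor power one week apart (*Functional biomarkers*). That is not a 12-month value, but at 0.97 the cost would be only 2/1.97 − 1 = 1.5%. Nothing in the article shows a moderate r for DXA or HR-pQCT, so the gain there may be small.

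**Naming ANOVA fits the design.** The vibration arm is re-randomized at month 12, which leaves three groups at 18 and 24 months, so a method for more than two groups is needed. That explains ANOVA beside the t-test, but not the missing covariate, since ANCOVA also handles three groups.

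**The analysis plan may say more.** It may, and a repeated-measures model, a key secondary visit and the standing of secondary p-values are commonly settled there. The choice of t-test and ANOVA is different: the article states it.

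**A stronger reading to avoid.** From the many parameters and visits in Table 2, together with "For all tests, we will use two-sided *p* values with an alpha ≤ 0.05 level of significance", a reader might infer that every parameter is tested at every visit and that a run of false positives is built in. The article does not say so. Table 2 lists when outcomes are measured, not which contrasts are tested, and nothing labels the secondary outcomes confirmatory. The number of tests is also a separate matter, because ANCOVA at each visit would leave it unchanged.

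**Conclusion.** The point holds as one of efficiency and consistency. The article names, for continuous secondary outcomes, a method that is in general less precise than the one it uses for the primary outcome, although the baselines are collected. BMD is treated in two ways depending on the visit.

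The cost is equivalent to about 33%, 18% or 5% more patients at r of 0.5, 0.7 or 0.9, and is negligible above 0.9. A one-standard-error baseline imbalance would move a change-score contrast by about 0.18 SD at r = 0.5 and 0.04 SD at r = 0.9 with 16 per arm. Both figures assume equal variances at baseline and follow-up, a linear relation between them, and correlations that the article does not supply. The primary analysis and the sample size are unaffected.

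**What to change.** In *Statistical methods and data managing*, replace the t-test and ANOVA for continuous secondary outcomes with the ANCOVA already planned for the primary outcome, using the outcome's own baseline value as covariate. Where the plan already allows log transformation, use the log scale for both outcome and baseline. Include BMD at 6, 18 and 24 months, so that BMD is analysed in one way throughout.

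State the groups compared: the two randomized arms up to month 12, and at 18 and 24 months the three groups created by re-randomization (no vibration, vibration continued, vibration stopped).

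The cost is one residual degree of freedom per model, a sentence of wording and slightly longer code in the same software. No new data are needed. Where r is very high, the change gains nothing and loses almost nothing.

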**Methods/design:**

PaVOS is a multicenter, assessor-blinded, superiority, two-armed randomized controlled trial (RCT).

Postmenopausal women (*n* = 40, aged 50 years and older) starting taking PTH 1-34 from outpatient clinics will be randomized and assigned to a PTH 1-34 + WBV-exercise group (intervention group), or a PTH 1-34-alone group (control group).

The intervention group will undergo WBV three sessions a week (12 min each, including 1:1 ratio of exercise: rest, 30 Hz, 1 mm amplitude) for a 12-month intervention period. Both the intervention and the control group will receive PTH 1-34 treatment (20 μg s.c. daily) for 24 months. After 12 months the WBV group will be re-randomized to stop or continue WBV for an additional 12 months.

The primary endpoint, bone mineral density (BMD), will be measured by dual-energy x-ray absorptiometry of the total hip and the lumbar spine.

Secondary endpoints, bone microarchitecture and estimated bone strength, will be assessed using high-resolution peripheral quantitative computed tomography (HR-pQCT) of the radius and tibia. Serum bone turnover markers (carboxy-terminal collagen crosslinks (CTX), amino-terminal propeptide of type-I collagen (P1NP), and sclerostin) and functional biomarkers (Timed Up and Go (TUG), Short Physical Performance Battery (SPPB), grip strength, and leg extension power) will be measured to assess the effect on bone turnover, muscle strength, balance, and functionality. Quality of life (EQ-5D), physical activity (IPAQ) and fear of falling (FES-I) will be assessed by questionnaires. Data on adherence and falls incidence will be collected.

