#### Study objectives

To determine if WBV in addition to standard PTH 1-34 treatment has a greater effect in osteoporotic patients compared to standard PTH 1-34 treatment alone on:BMDBone microarchitectureMarkers of bone formation and resorptionMuscle function and balanceTo assess the safety and adherence to WBV in osteoporotic patients

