### Randomization

After informed consent and collection of baseline data, participants will be randomized into two groups: PTH 1-34 treatment alone or PTH 1-34 treatment + WBV (Fig. 2). The randomization is a web-based, computer-generated block randomization with no stratification. Block size is created by a data manager and the size is unknown to the investigators until the end of the study. Allocation will be concealed to the participants and the investigators until after collection of baseline data.

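### The plan names a matched-pairs signed-rank test for non-normal secondary outcomes, and that test cannot compare two unmatched randomised arms

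*Protocol article*

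**What the plan says.** Statistical methods and data managing fixes ANCOVA on percentage change, adjusted for baseline, for the primary outcome. It then turns to the rest: "For secondary outcomes we will use a chi-squared test for binary outcomes", with ANOVA and the t test for continuous outcomes. Where a continuous outcome is not normally distributed, the fallback is log transformation or Wilcoxon's "match-pairs signed-rank test and the Kruskal-Wallis test". It does not say which of these tools serves the comparison between arms and which, if any, serves change within an arm. The rank-sum (Mann-Whitney) test is not named.

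Three other places bear on the choice of test:

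- Study objectives asks whether WBV added to PTH 1-34 "has a greater effect in osteoporotic patients compared to standard PTH 1-34 treatment alone". That is a question between arms.
- Randomization describes a "web-based, computer-generated block randomization with no stratification". No participant in one arm is matched to a participant in the other.
- The Abstract states: "Both the intervention and the control group will receive PTH 1-34 treatment". Any response to PTH 1-34 is therefore common to the arms.

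**The concern.** A signed-rank test needs pairs. The only natural pairs in this trial are the baseline and follow-up values of one participant. On those pairs the test asks whether an arm changed, not whether WBV added anything.

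The position of the test in the text suggests a slip. ANOVA and the t test are listed for continuous outcomes, followed by two rank tests for the non-normal case. Kruskal-Wallis is the rank counterpart of ANOVA. The signed-rank test sits where the rank counterpart of the two-sample t test belongs, and that is the rank-sum test. The sentence that commits the analysis to the arm-versus-arm contrast ("The intervention arm (PTH + WBV) is compared against the control arm for all primary analyses") speaks only of primary analyses, so it does not confine the paired test to a descriptive role.

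At stake is the reading of the secondary outcomes in Table 2 that prove non-normal, among the bone markers, HR-pQCT measures, physical tests, EQ-5D and FES-I. The section on serum bone turnover markers itself says that PTH 1-34 affects bone turnover. Change in those markers within each arm is thus expected with no WBV effect at all.

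**Working it through.** **Inputs from the protocol article.** Sample size determination gives 16 evaluable participants per arm (20 enrolled), a difference of 11% − 9% = 2 points, an SD of 2%, 80% power and 20% dropout. Statistical methods and data managing gives two-sided alpha 0.05.

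**The plan's own figure.** n per arm = 2(1.96 + 0.84)² × (SD/difference)² = 2 × 7.85 × (2/2)² = 15.7, so 16 per arm and 32 in total; 32/0.8 = 40. The stated sample size reproduces. It is used here only to set the number per arm, because the plan states no figure for the rank tests.

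**Assumed input.** The article gives no shared response for the secondary outcomes, so a range from 0 to 4.5 SD was used. The top of the range is the planning figure for BMD in the control arm, 9%/2% = 4.5 SD. BMD is the primary outcome, so this is only a reference point.

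**Simulation.** Each setting had 4,000 trials. Changes from baseline were skewed (gamma, shape 4, scaled to SD 1), with the same mean change in both arms and no WBV effect. The entries are the proportions with p < 0.05.

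| n per arm | Shared change (SD) | Signed-rank on change, WBV arm only | Kruskal-Wallis between arms | Signed-rank, arms paired arbitrarily |
|---|---|---|---|---|
| 16 | 0 | 0.0655 | 0.0448 | 0.0420 |
| 16 | 0.5 | 0.3658 | 0.0475 | 0.0420 |
| 16 | 1 | 0.9845 | 0.0455 | 0.0418 |
| 16 | 2 | 1.0000 | 0.0445 | 0.0413 |
| 16 | 4.5 | 1.0000 | 0.0463 | 0.0440 |
| 20 | 0 | 0.0680 | 0.0468 | 0.0453 |
| 20 | 0.5 | 0.4743 | 0.0468 | 0.0470 |
| 20 | 1 | 0.9985 | 0.0483 | 0.0468 |
| 20 | 2 | 1.0000 | 0.0470 | 0.0485 |
| 20 | 4.5 | 1.0000 | 0.0553 | 0.0540 |

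The simulation error of a true 5% rate is √(0.05 × 0.95/4000) = 0.0034, so the Kruskal-Wallis column is consistent with 5% throughout. The rank-sum test without continuity correction gave the same rates as Kruskal-Wallis in every row, as it must with two groups.

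**Check on the shape of the distribution.** With normal instead of skewed changes, 16 per arm and a shared change of 1 SD, the signed-rank test within the WBV arm rejected in 94.6% of 4,000 trials and the rank-sum test between arms in 4.7%.

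**Reading.** The within-arm test responds to the shared change and says nothing about WBV. The between-arm rank test holds its level whatever the shared change. Pairing participants arbitrarily across arms would not pick up the shared change, but such pairs have no basis in the design, and unequal dropout would leave some participants without a partner.

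**The case against.** The strongest reply is that the sentence already contains valid routes. Kruskal-Wallis compares independent groups and with two arms is equivalent to the rank-sum test. Log transformation followed by a t test or ANOVA is also a comparison between arms. Participants are measured repeatedly, so a signed-rank test can properly describe change within an arm, and the authors may have meant only that. This stands in part. It rules out saying that the plan has no valid fallback. It does not give the signed-rank test a role, because no objective about change within an arm is stated and nothing in the sentence divides the work between the two rank tests.

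A reader might infer two stronger points, and the article supports neither:

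- **That the trial will report the shared PTH 1-34 response as a WBV effect.** The article nowhere says that within-arm p values will be read as the treatment effect, or that significance in one arm will be set against its absence in the other. The rejection rates above apply only if someone reads them so.
- **That log transformation fails because Table 2 defines most endpoints as changes, which can be zero or negative.** The Table 2 footnote does define the symbol as "change from baseline; Time is measured in months", but the text does not say that the change itself is logged. Logging the raw values and then adjusting for baseline is an ordinary reading, and an article may leave that detail to the full plan.

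**Conclusion.** Wrong as written, with moderate to low severity. The signed-rank test cannot make the randomised comparison, and the article lists it, without a role, among the tests for non-normal secondary outcomes.

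The harm is conditional on a within-arm result being taken as evidence for WBV. In that case the false-positive rate would be about 37% (16 per arm) to 47% (20 per arm) at a shared change of 0.5 SD, and about 95% or more at 1 SD. A between-arm rank test stays near 5%. These rates rest on assumed shared changes and on the simulated distributions. The conclusion that the test does not fit the design rests on neither.

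The reach is limited to continuous secondary outcomes that prove non-normal. The primary ANCOVA and the sample size are untouched.

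**What to change.** Replace the fallback sentence with one that gives each test its role, for example:

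> For non-normally distributed continuous secondary outcomes, the two arms will be compared with the Wilcoxon rank-sum (Mann-Whitney) test, and the three groups after the 12-month re-randomisation with the Kruskal-Wallis test.

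Kruskal-Wallis may also be kept for two arms, since it is equivalent there. For skewed markers, a baseline-adjusted ANCOVA on log-transformed raw values is an equally acceptable route and matches the approach to the primary outcome. Delete the signed-rank test, or state that it only describes change within an arm and is not evidence on WBV.

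The cost is one sentence in the analysis section or the analysis plan, settled before the outcome data are analysed. No new data and no change in sample size are needed.
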